### **6.1.3 Usage Data of the online program**

The following usage data will be collected by the online program for each participant: individual progress in the four modules, dates and frequencies of logins and time spent in the online program. In the condition with individualized support, the correspondence with the psychologist will be stored as well, and after manually removing any potentially identifying information, will be used for content analyses of topics in support messages in pseudonymized form.

### **6.1.4 Data collection quality**

To improve data completeness the participants will get repeated E-Mail reminders, if they don't fill in the questionnaires at T1, T2 or T3. For completing all measurements, the caregivers get a compensation in the form of a 30€ voucher (10€ for each measurement point, to be traded in at a large number of services).

If participants choose to end participation in the study, they will be asked to provide their reasons. Participants no longer interested in the intervention will nonetheless be asked to complete all measurements.

To promote data quality, data will be monitored during data collection. Data monitoring will consist of blinded reviews of the data for programming errors (e. g., data ranges different than expected) as well as for missing data. If problems are detected, corresponding steps will be taken (e. g., additional efforts to reach participants for each measurement if a large proportion of data is found to be missing).

#### **6.1.5 Collection of qualitative interview data**

At T2 and possibly T3, individual participants (caregivers and depressed persons) will be selected based on stratification criteria (based on theoretical sampling with both a priori criteria such as type of relationship to depressed person as well as criteria emerging in the analysis process) and interviewed by telephone for approximately 60-90 minutes. The interviews are conducted by trained psychological personnel using a semi-structured interview guideline. The contents of the interviews with caregivers focus on the experiences with the online self-help program, the support conditions, everyday life experiences and the interaction with the depressed person as well as potential changes brought about by the intervention. The contents of the interviews with depressed persons focus on the depressed persons' experiences of potential changes in the caregivers' behavior and their interactions. The semi-structured interview form is intended to capture the subjective perception of the participants. It is characterised by a predetermined catalogue of questions with the flexibility to elaborate topics that arise during the interview or change the order of questions to follow the flow of the conversation. The interview consists of a warm-up phase and five thematic blocks. After the general experiences with the coach and the supportive messages, specific experiences with the topic areas of all four modules will be asked. There are a few narrative prompts for each thematic block, supplemented by follow-up questions that are only explicitly asked if the respective aspects do not appear in the participants' spontaneous narrative or report. The content of the interviews is recorded in the form of audio recordings. Before further analysis, the audio recordings are transcribed into text, removing or changing names and other potentially identifying information to achieve pseudonymized data.

## **6.2 Data management**

### **6.2.1 Storage of data**

All data collected in the context of this study will be collected electronically only. Descriptive data of the participants and usage data (e.g. login duration and frequency) will be recorded, as well as data from questionnaire surveys. The data collection takes place on the website of the online self-help-program, which is created and operated (hosting, account management) by the consortium partner H6 Kommunikationsagentur ([name]) under the leadership of [name]. For technical and administrative processes H6 Kommunikationsagentur has access to all data collected in the study. All data collected in the study will be stored on a server of the company Mittwald CM Service GmbH & Co. KG ([name]).

Compliance with the European General Data Protection Regulation (GDPR: EU Regulation 2016/679) is secured through a data processor agreement (AV-Vertrag) between Mittwald and the University Clinic. The same applies for other potential contractors of the consortium partners, while shared and individual responsibilities between the consortium partners H6 Kommunikationsagentur and the University Clinic will be defined in a contract of shared responsibilities (according to Art. 26 DS-GVO).

Data files will be archived in order to comply with the data protection requirements and deleted completely after 10 years. The required archiving periods of at least five years after publications will be adhered to.

The correspondence between the participants in the condition with individualized support and the psychologist will be transferred by encrypted connection to secure clinic servers for storage and further processing. Before the evaluation of this data, the correspondence are checked by study staff to see whether information appears that allows conclusions to be drawn about the caregiver or the depressed person (e.g. names, addresses, ...). If this is the case, the information is deleted from the correspondence.

The contents of the interviews are divided into sensitive audio recordings on the one hand, which remain on protected clinic servers, and pseudonymized transcripts (names and other information that make a person identifiable are changed during transcription) on the other hand for the further research process. Strict separation of the subjects' names or audio recordings and the other data collected ensures pseudonymized data processing. In case that subjects request a complete deletion of

their own data, all personal data will be deleted. Accordingly, deletion includes all demographic data, contact data and data of inclusion and exclusion criteria as well as potential interview recordings. Questionnaire data, pseudonymized psychological correspondence and transcribed interview data, that has been produced until then, will be analyzed completely anonymized.

### **6.2.2 Data Transfer**

The stored data will be compiled for analysis by the consortium partner H6 Kommunikationsagentur and transferred only to the Institute of Medical Biometry and Statistics of the University Medical Center Freiburg (IMBI) and the study direction. Data transfer to other parties is not intended.

In order to analyse the data, the data records will be transmitted to the Institute of Medical Biometry and Statistics in pseudonymized form. During data collection the Institute of Medical Biometry and Statistics gets access to the data, to monitor the data quality. For further monitoring, the principal investigator can request a data transfer of the pseudonymized data at any time. Data transfer will be carried out only electronically via encrypted data connections and only on the instructions of the principal investigator.

### **6.2.3 Data protection/Data security**

To participate in the study, the participants register with a confirmed e-mail address and a secure password. The use of the online program, messaging system and the associated data collection will take place exclusively in the protected login area of the online program. All data collected will be stored by the Mittwald company. The Mittwald Company undertakes to perpetually treat the collected data confidentially and to use it only for the purpose of conducting the present study. Personal data will be processed in such a way that the data can no longer be assigned to a specific subject without additional information (pseudonymization).

The company Mittwald gives a written undertaking to comply with the European General Data Protection Regulation (GDPR: EU Regulation 2016/679) and with the technical and organizational measures being necessary and appropriate for their compliance, which are as follows:

|                                                                                        |                                                                                                                                                                                                                                                                                                                                                                                                                                                                                                                                                                                                                                                                  |
|----------------------------------------------------------------------------------------|------------------------------------------------------------------------------------------------------------------------------------------------------------------------------------------------------------------------------------------------------------------------------------------------------------------------------------------------------------------------------------------------------------------------------------------------------------------------------------------------------------------------------------------------------------------------------------------------------------------------------------------------------------------|
| 
No unauthorized access to technical facilities
                                  | 
 
– The company building is divided into different areas of access.
 
– Visitors must register at the reception and are picked up by their contact person.
 
– Access to all data processing systems will be completely denied to unauthorized persons.
 
– The access of any person (including employees) must be approved in advance by authorized personnel and is verified by checks on persons.
 
– All accesses and premises of the data processing systems will be monitored by cameras and controlled by electronic locking systems.
 
– All access will be recorded.
 
 |
| 
Access controls to important facilities (hardware, operating systems, software)
 | 
 
– The access to the data processing systems is secured by a user and rights administration. Employees can only view, use, process or delete the data required for their tasks.
 
– Accesses to the data processing systems will be logged.
 
– When leaving the workplace, the system is blocked by a screensaver and can be unlocked only by entering the password.
 
– Accordingly, at the time of recruitment every employee is committed to confidentiality and compliance with data protection. A violation would result in instant dismissal and a criminal complaint.
 
              |
| 
Control of data transmission
                                                    | 
 
– Personal data will be transmitted only electronically via encrypted data connections, so that they cannot be read, copied, changed, or removed by unauthorized persons.
 
                                                                                                                                                                                                                                                                                                                                                                                                                                      |

|               |                                                                                                                                                     |
|---------------|-----------------------------------------------------------------------------------------------------------------------------------------------------|
|               | 
 
– Data media that are no longer required or defective will be disposed of by a certified company.
 
 |
| Data Transfer | All Data transfer will be encrypted (encrypted Internet connections using TLS/SSL).                                                                 |

If, despite the detailed technical and organizational measures taken, there should be a serious disturbance of operating procedures, a suspicion of data protection violations or other irregularities in the processing of personal data, the consortiums partners are obliged to inform the study direction immediately and to jointly decide on further proceedings.

All data processing will be carried out in Germany or a member state of the European Union only.

Mittwald Company also implements a data protection management system for the regular monitoring, assessment and evaluation of data protection and the effectiveness of the established technical and organizational measures.

#### **6.2.4 Data integrity**

To ensure data integrity, it can be checked retrospectively at any time whether and by whom personal data has been entered, changed or removed in data processing systems. The entry, modification or deletion of personal data is logged with the identification of the responsible employee.

Additionally, the protection of personal data against accidental destruction or loss is ensured (e.g. by RAID systems, replacement hardware, surge protection, UPS systems, emergency generator, extinguishing systems). Also, measures will be taken to ensure the quick restoration of availability and access to personal data in the case of a physical or technical incident (e.g. by daily backups).

### **6.3 Statistical methods**

#### **6.3.1 Biostatistical planning and analysis**

Before the start of the final analysis, the details of statistical analysis left open in the trial protocol will be described in a statistical analysis plan (SAP). At the latest, the SAP will be completed during a blinded review of the trial data, i.e. without looking at the randomized intervention for individual caregivers. If the SAP contains any changes to the analyses outlined in the trial protocol, they will be marked as such, and reasons for amendments will be given.

Throughout, emphasis will be given to reporting of effect estimators with two-sided 95%-confidence intervals rather than p-values whenever possible, which will be considered statistically significant if below 5% for tests of equality. However, confirmatory statistical testing will be restricted to the analysis of the primary outcome, to be followed by descriptive reporting of other trial results.

All programming for statistical analysis will be performed with the Statistical Analysis System (SAS) or with R.

### **6.3.2 Main analysis of primary outcome**

**Model:** The primary efficacy analysis will be performed in the full analysis set (FAS) according to the intention-to-treat (ITT) principle. Therefore, all randomized caregivers will be analysed in the assigned treatment arms, irrespective of treatment adherence and whether they refuse or discontinue the intervention. The effects of allocation to IND, AUT and TAU with respect to the primary endpoint, change in K-10 score from baseline to four weeks after randomisation, will be estimated and tested in a linear regression model, and the corresponding two-sided 95%-confidence intervals will be reported. The model will include randomized treatment (IND, AUT, TAU), age (years, 18-40, 41-65,  $\geq 66$ ), gender (female, male; for diverse, see end of paragraph), caregiver's relation with depressed person (parent, child, partner, other), and K-10 baseline scores as independent variables. Since very few caregivers of diverse gender are expected, they will be assigned alternately to the groups of females and males in the primary analysis of intervention effects. They will be analysed separately in secondary analyses exploring the effect of gender.

**Sequential testing:** Following a sequential closed testing procedure to ensure a multiple type I error rate of 5%, confirmatory comparisons of randomized treatment arms will proceed until the first occurrence of a non-significant result at the nominal 5% level, followed by descriptive reporting of all subsequent analyses. The two-sided tests of equality of means of two treatment arms will be based on the two-sided 95% confidence interval for the difference in mean change from baseline estimated from the linear regression model. Treatment arms will be compared in the following order: IND versus TAU, AUT versus TAU, IND versus AUT. Although it is hypothesized and subjected to confirmatory testing that IND is superior to AUT, equality is also deemed possible. In a secondary descriptive analysis, demonstration of non-inferiority of AUT compared to IND will also be attempted. If the lower limit of the two-sided 95%-confidence interval for the difference of mean K-10 changes from baseline (IND minus

AUT) is greater than -0.62 points, this will be interpreted as non-inferiority. The non-inferiority margin was derived as follows: For caregivers of depressed persons, the expected standard deviation of K-10 scores is in between that of patients (SD: 4.6 points) and students (SD: 7.8 points) seen in the German norm sample (Giesinger et al., 2008). Therefore, a standard deviation of 6.2 score points is expected. Assuming a correlation of 0.5 between baseline and post-intervention K-10 scores, the change from baseline has also a standard deviation of 6.2 points, and using Cohen's  $d=0.1$  as non-inferiority margin gives 0.62 points.

**Handling of missing values:** Multiple imputation will be employed to replace missing values. Imputation will be done per randomized treatment arm, using baseline data and post-baseline information according to a Treatment Policy Strategy as described by Polverejan and Dragalin (2020) and Guizzaro et al. (2020). The results will be combined using Rubin's rules for multiple imputation. The details will be fixed in the statistical analysis plan.

**Assumptions:** The resulting estimators assume that caregivers with missing outcome data have outcomes similar to those of subjects with similar baseline data and treatment adherence who provide their outcome data.

**Interim analysis:** As described in section 7.1, an interim analysis is not considered necessary for this study. The lead investigator will monitor the progress of the study with regard to safety-relevant development as detailed in section 7.2.

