### 3.3 Hypothesis

**Primary hypotheses:** The online self-help program with individualized (IND) or automated (AUT) e-mail support reduces the unspecific mental distress of the caregivers (as an indicator for the risk of mental diseases) as compared to TAU. In a comparison of the two kinds of support, the individualized support will be more effective than the automated support.

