## 4.6 Sample Size

The numbers of caregivers to be randomized to the respective intervention and control groups IND:AUT:TAU are  $n=500:500:250$ . This accounts for an expected 20% rate of missing K-10 outcome measurements at T2 – yielding an expected  $n=400:400:200$  non-missing primary outcomes – and for the following power considerations. Randomized groups will be compared using a sequential closed test procedure: To guarantee a multiple significance level of 5%, confirmatory statistical testing at nominal significance level  $\alpha=5\%$  will continue until the first non-significant result. Pairwise comparisons between randomized groups will be performed via calculation of a two-sided 95% confidence interval for the difference of means, for which exclusion of a zero difference is equivalent to rejection of the null hypothesis in an unpaired t-test of equal means at two-sided significance level  $\alpha=5\%$ . The first and second statistical test to reject equalities  $IND=TAU$  and  $AUT=TAU$  of mean pre-to-

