post-(T2-T0) K-10 changes at significance level  $\alpha=5\%$  will implement the primary objective by comparing online self-help program interventions with control; they have a power of  $1-\beta\approx 99\%$  given a medium effect size (Cohen's  $d$ ) of  $d=0.5$ , and of  $1-\beta=93\%$  if  $d=0.3$ . Such effect sizes appear to be realistic based on a single-arm pre-post comparison following a psychoeducation program which yielded  $d=1.1$  for a shorter version of the primary outcome scale, the K-6 scale (Katsuki et al., 2011). As regards the third comparison among the two online self-help program intervention groups IND and AUT, both superiority of IND over AUT and, to a lesser degree, equality of IND and AUT can appear realistic; it would be worth-while to reject equality  $IND=AUT$  or inferiority of AUT. The pairwise test comparing the two online self-help program intervention groups to reject  $IND=AUT$  has a power of  $1-\beta=81\%$ , given a small effect size of  $d=0.2$ . Confirmatory testing will stop after this comparison. Given equal means  $IND=AUT$  ( $d=0$ ), it would also be of interest to reject inferiority of AUT ( $d=-0.1$ ), i.e. to demonstrate non-inferiority of the less costly intervention AUT compared to the more costly intervention IND at one-sided significance level  $\alpha=2.5\%$ . The power to achieve this secondary objective, i.e. to reject such a small inferiority, is  $1-\beta=29\%$ . Higher recruitment targets to achieve greater power were dismissed for reasons of feasibility. The scenarios considered are summarized in terms of standardized group means shifted towards 0 for the TAU group in the table below (nQuery V8.3.1.0, module MGT0U).

| Standardised mean
IND,AUT,TAU | Power to reject a single null hypothesis (n=400:400:200): |         |         |             |
|----------------------------------|-----------------------------------------------------------|---------|---------|-------------|
|                                  | IND=TAU                                                   | AUT=TAU | IND=AUT | AUT inf IND |
| 0.5, 0.3, 0                      | 99%                                                       | 93%     | 81%     | <1%         |
| 0.5, 0.5, 0                      | 99%                                                       | 99%     | 5%      | 29%         |
| 0.3, 0.3, 0                      | 93%                                                       | 93%     | 5%      | 29%         |

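### Making IND vs AUT wait for a significant AUT vs TAU is valid but not needed for the 5% multiple level, and it costs power for a comparison listed among the primary hypotheses

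*Protocol*

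**What the plan says.** Protocol section 4.6 sets up a sequential closed test procedure at nominal 5% in which confirmatory testing "will continue until the first non-significant result". Section 6.3.2 repeats that comparisons "proceed until the first occurrence of a non-significant result at the nominal 5% level" and fixes the order: "Treatment arms will be compared in the following order: IND versus TAU, AUT versus TAU, IND versus AUT". Each test "will be based on the two-sided 95% confidence interval for the difference in mean change from baseline", estimated from a linear regression that includes baseline K-10.

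The third comparison is confirmatory. Section 3.3 places it under the primary hypotheses: "In a comparison of the two kinds of support, the individualized support will be more effective than the automated support".

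Section 4.6 gives 81% power for IND=AUT at d=0.2. The table there heads its columns as power for a single null hypothesis. It covers three sets of standardised means (IND, AUT, TAU): 0.5/0.3/0, 0.5/0.5/0 and 0.3/0.3/0. No probability of passing the whole sequence is given, and AUT lies at least 0.3 above TAU in every row.

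**The concern.** Under the fixed order, IND vs AUT can be confirmed only if AUT has first beaten TAU. If AUT misses significance against TAU, the comparison of the two kinds of support becomes descriptive, however large the difference. So when the advantage of IND over AUT arises because AUT does little, that advantage becomes harder to confirm as it grows.

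This would be an acceptable price if the gate were needed to hold the 5% multiple level. It is not. The protocol calls the procedure closed, and closure for three pairwise equalities permits a less restrictive rule at the same level.

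**Working it through.** **Inputs.** Section 4.6: n=400:400:200 evaluable (500:500:250 less 20% missing) and standardised means with SD 1. Sections 4.6 and 6.3.2: two-sided 5%, the test order and the stopping rule. Section 6.3.2: baseline K-10 in the model and an assumed baseline-to-post correlation of 0.5.

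**1. The protocol's own figures.** Power ≈ Φ(d/SE − 1.96), with SE = √(1/n₁ + 1/n₂).
- IND vs TAU: SE = √(1/400 + 1/200) = 0.0866; 0.5/0.0866 = 5.77; power above 99.9% (stated 99%).
- AUT vs TAU: 0.3/0.0866 = 3.46; power 93.4% (stated 93%).
- IND vs AUT: SE = √(2/400) = 0.0707; 0.2/0.0707 = 2.83; power 80.7% (stated 81%).

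The noncentral t gives 93.3% and 80.6% for the last two. The stated figures reproduce.

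**2. Is the second gate needed?** Any two of the three equalities imply the third, so the only intersection hypothesis is IND=AUT=TAU.
- If IND=TAU is true, nothing can be rejected unless the first test errs, which has probability 5%.
- If IND=TAU is false, at most one of AUT=TAU and IND=AUT is true, so testing each at 5% gives at most a 5% chance of a false rejection.

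Simulated familywise error of this rule (2 million trials per configuration) was 5.0% with all means equal (0/0/0), with only IND=AUT true (0.5/0.5/0), with only AUT=TAU true (0.5/0/0) and with only IND=TAU true (0/0.5/0). The other configurations checked did not exceed 5.0%.

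**3. Chance of confirming IND vs AUT.** The statistics for AUT−TAU and IND−AUT share the AUT mean with opposite signs. Their correlation is −(1/400)/(0.0866 × 0.0707) = −0.41. In scenario 0.5/0.3/0, simple multiplication would give 0.934 × 0.807 = 75.4%; simulation of all three correlated tests gives 74.4%.

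For the adjusted columns, the SD of change at correlation 0.5 equals the SD of a single score, √(2(1 − 0.5)) = 1. The residual SD after baseline adjustment is √(1 − 0.5²) = 0.866, so every standard error shrinks by that factor. The other covariates are taken to explain nothing further, and imputation to add no information.

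| IND/AUT/TAU | Unadjusted, gate | Unadjusted, no gate | Adjusted, gate | Adjusted, no gate |
|---|---|---|---|---|
| 0.5/0.3/0 (protocol) | 74.4% | 80.8% | 88.4% | 90.4% |
| 0.4/0.2/0 (assumed) | 47.5% | 80.6% | 67% | 90% |
| 0.5/0.1/0 (assumed) | 21.2% | >99% | 27% | >99% |

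Here, no gate means gated only on IND vs TAU. The protocol's other two rows have IND=AUT, so there is no true difference to confirm.

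**4. Sensitivity to the correlation.** In scenario 0.5/0.3/0, the adjusted power with the gate is 91%, 86% and 83% at assumed correlations of 0.4, 0.6 and 0.7.

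**The case against.** The strongest reply is that the protocol contains no error here. A fixed sequence at 5% is valid, and the order can be read as deliberate. Section 3.2 frames the primary question as either form of support against TAU. Section 4.6 says the first two tests implement the primary objective, and treats equality of IND and AUT as also possible. If AUT fails against TAU, the IND vs AUT difference is still reported with its 95% confidence interval; only the confirmatory label is lost. All of this stands. It does not justify the gate, because the alternative leaves both TAU comparisons, their order of priority and their power as they are. Nothing is given up to gain the power.

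Three stronger readings are tempting, and the document does not support them.
- A reader might infer that 81% is wrong and should be 74%. The table is labelled as power for a single null hypothesis, and 81% is right under that label; substituting 74% would make the column wrong.
- A reader might take 74% as the power of the planned analysis. It belongs to an unadjusted t-test. Under the planned baseline-adjusted model at correlation 0.5, the sequence confirms IND vs AUT with 88% probability in the same scenario, and the gate costs 2 points.
- A reader might infer that the plan's own assumptions lead to a collapse in power. They do not. The large losses need an AUT effect below every value tabulated in section 4.6.

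**Conclusion.** The point holds as an avoidable loss of power in a valid procedure. It is not an inflated error rate and not a miscalculation.

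In the one tabulated scenario where IND differs from AUT, the loss is about 6 percentage points unadjusted and about 2 adjusted. With a weaker AUT it is large and adjustment does not remove it: for 0.4/0.2/0 it is about 33 points unadjusted and 23 adjusted, and for 0.5/0.1/0 it exceeds 70 points either way. Those two scenarios are assumptions made here. They are not far-fetched: section 3.1 describes automation of human guidance as at an early stage, and section 4.6 supports its effect sizes with a single-arm pre-post result.

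The figures rest on 400:400:200 evaluable caregivers, equal variances, normal test statistics and, for the adjusted columns, the protocol's correlation of 0.5. The logical argument that the gate is unnecessary rests on none of these.

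**What to change.** Amend sections 4.6 and 6.3.2 so that IND vs TAU is tested first at two-sided 5% and, if it is significant, AUT vs TAU and IND vs AUT are each tested at two-sided 5%, neither depending on the other. State the reason: once IND=TAU is false, the two remaining equalities cannot both be true.

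Section 6.3.1 requires changes made in the SAP to be marked and justified, with the SAP completed at the latest during the blinded review; section 8.2 gives the amendment route. Because the trial is open-label, the change should be dated and in place before that review is completed.

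The cost is a few sentences. No alpha, sample size or power for either comparison with TAU is lost.

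Keep the 81% in section 4.6 as single-test power. If the sponsor prefers the fixed order, add beside it that the probability of passing the whole sequence in scenario 0.5/0.3/0 is 74% (unadjusted), so that readers can see what the order costs.
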